## Section: 2. Protocol Synopsis

|                             |                                                                                                                                                                                                                                                                                                                                                                                                                                                                                                                                                                                                                                                                                                                                                                                                                                                                                                                                                                                                                                                                                                                                                                                                                                         |
|-----------------------------|-----------------------------------------------------------------------------------------------------------------------------------------------------------------------------------------------------------------------------------------------------------------------------------------------------------------------------------------------------------------------------------------------------------------------------------------------------------------------------------------------------------------------------------------------------------------------------------------------------------------------------------------------------------------------------------------------------------------------------------------------------------------------------------------------------------------------------------------------------------------------------------------------------------------------------------------------------------------------------------------------------------------------------------------------------------------------------------------------------------------------------------------------------------------------------------------------------------------------------------------|
| Protocol name        | The effects and safety of Bushen Yijing Fang (BSYJF) reduces hip fractures risk factors in late postmenopausal women with osteopenia: A long-term follow-up, randomized, double-blind and placebo-controlled trial                                                                                                                                                                                                                                                                                                                                                                                                                                                                                                                                                                                                                                                                                                                                                                                                                                                                                                                                                                                                               |
| Sponsor                     | Shanghai Shuguang Hospital                                                                                                                                                                                                                                                                                                                                                                                                                                                                                                                                                                                                                                                                                                                                                                                                                                                                                                                                                                                                                                                                                                                                                                                                              |
| Indication                  | Late postmenopausal women with osteopenia                                                                                                                                                                                                                                                                                                                                                                                                                                                                                                                                                                                                                                                                                                                                                                                                                                                                                                                                                                                                                                                                                                                                                                                               |
| Purpose                     | To evaluate long-term efficacy of BSYJF on hip fracture risk factors in late postmenopausal women with osteopenia.                                                                                                                                                                                                                                                                                                                                                                                                                                                                                                                                                                                                                                                                                                                                                                                                                                                                                                                                                                                                                                                                                                                      |
| Design               | Randomized, 36-month, double-blind and placebo-controlled trial with 10 years extension follow-up                                                                                                                                                                                                                                                                                                                                                                                                                                                                                                                                                                                                                                                                                                                                                                                                                                                                                                                                                                                                                                                                                                                                |
| Simple size                 | 140 subjects (70 per group)                                                                                                                                                                                                                                                                                                                                                                                                                                                                                                                                                                                                                                                                                                                                                                                                                                                                                                                                                                                                                                                                                                                                                                                                             |
| Setting                     | Two sites                                                                                                                                                                                                                                                                                                                                                                                                                                                                                                                                                                                                                                                                                                                                                                                                                                                                                                                                                                                                                                                                                                                                                                                                                               |
| Intervention time    | From 2000-01-01 To 2004-12-31                                                                                                                                                                                                                                                                                                                                                                                                                                                                                                                                                                                                                                                                                                                                                                                                                                                                                                                                                                                                                                                                                                                                                                                                    |
| Eligibility criteria | 
Inclusion:
 
 
1. Women with at least 10 years after natural menopause, and aged from 55 to 69 years;
 
2. Osteopenia at least 12 months (T-score between -2.5 and -2 SD at femoral neck).
 
 
Exclusion:
 
 
1. Who had been diagnosed as having a neurological or musculoskeletal disorder, or coexisting chronic diseases;
 
2. Who have taken estrogen and calcitonin, fluoride, bisphosphonates, or adrenocortical hormone within one year;
 
3. Who had been took <math>\geq 4</math> prescription medications;
 
4. has environmental hazards for falls or tripping;
 
5. has impairment in gait;
 
6. has postural hypotension: drop in systolic blood pressure <math>\geq 20</math>mmHg or to <math>< 90</math>mmHg on standing;
 
7. has impairment in transfer skills or balance;
 
8. has impairment in leg or arm muscle strength or range of motion (hip, ankle, knee, shoulder, hand, elbow) ;
 
9. has ALT or AST levels greater than 50% of upper normal limit; serum creatinine levels greater than 133<math>\mu</math>mol/l or
 
 |

|                                   |                                                                                                                                                                                                                                                                                                                                                                                                                                                                                                                                                                                                                                                                                                                                                                                                                                                                                                                                                                            |
|-----------------------------------|----------------------------------------------------------------------------------------------------------------------------------------------------------------------------------------------------------------------------------------------------------------------------------------------------------------------------------------------------------------------------------------------------------------------------------------------------------------------------------------------------------------------------------------------------------------------------------------------------------------------------------------------------------------------------------------------------------------------------------------------------------------------------------------------------------------------------------------------------------------------------------------------------------------------------------------------------------------------------|
|                                   | 
1.5 mg/dl.
 
Additional exclusion criteria have been defined to protect subjects who have experienced a large bone loss or fragility fracture during the initial 36 month treatment phase of the study.
                                                                                                                                                                                                                                                                                                                                                                                                                                                                                                                                                                                                                                                                                                                                                 |
| Drug administration               | 300mg element calcium daily with either BSYJF capsules (3 capsules per time, 3 times per day) or placebo.                                                                                                                                                                                                                                                                                                                                                                                                                                                                                                                                                                                                                                                                                                                                                                                                                                                                  |
| Study period               | 36-month with 10 years extension follow-up                                                                                                                                                                                                                                                                                                                                                                                                                                                                                                                                                                                                                                                                                                                                                                                                                                                                                                                          |
| Endpoints                  | 
Endpoints are to be evaluated for BSYJF versus placebo.
 
Primary endpoint:
 
 
1. Number of falls at month 36.
 
 
Secondary endpoints:
 
 
1. Change from month baseline at month 36 in femoral neck BMD;
 
2. Change from month baseline at month 36 in lean mass of left thigh;
 
3. Change from month baseline at month 36 in TUG test;
 
4. Change from month baseline at month 36 in biomarkers of bone turnover (osteocalcin and deoxypyridinoline).
 
5. Change from month baseline at month 36 in endometrial thickness;
 
6. Change from month baseline at month 36 in estradiol;
 
7. Nature, frequency and severity of adverse events and their relationship to treatment.
 
 
Additional endpoint:
 
8. Number of falls at the end of 10 years extension follow-up.
 |
| Statistical considerations | 
All the analyses will use all randomly assigned patients under ITT principle. For patients missing data after the baseline, the LOCF approach use to analyze the longitudinal data. The number of falls at month 36 and adverse events will perform by chi-square test. Kaplan–Meier analysis will be calculated in order to demonstrate differences in number of fallers over time. The time to first fall will be analyzed using a Cox regression
                                                                                                                                                                                                                                                                                                                                                                                                                                                                                                                 |

|  |                                                                                                                                                                                                                                                                                                                                                                                                                                                                                                    |
|--|----------------------------------------------------------------------------------------------------------------------------------------------------------------------------------------------------------------------------------------------------------------------------------------------------------------------------------------------------------------------------------------------------------------------------------------------------------------------------------------------------|
|  | 
analysis providing a 95% confidence interval. Repeated-measures ANOVA analysis should be carried out between two groups and four times (baseline, 12, 24 and 36 months). Within-subjects results will be used t-test on the mean percentage change from the baseline value. All tests will be used two-sided and set at the 5% level.
 
Additional analysis:
Number of falls at the end of 10 years extension follow-up will be performed by chi-square test.
 |
|--|----------------------------------------------------------------------------------------------------------------------------------------------------------------------------------------------------------------------------------------------------------------------------------------------------------------------------------------------------------------------------------------------------------------------------------------------------------------------------------------------------|

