#### With:

A fall is defined as any event that led to an unplanned, unexpected contact with a supporting surface. Falls resulting from pathologic fracture, major trauma or facial trauma, and/or unavoidable hazards such as transient ischemic attacks, chair collapsing or cerebrovascular accidents will be excluded. A faller is defined as the participants sustained at least one fall or more. Information about new falls while on study will be documented using form, included the date of fall and related-injury. The number of falls is accumulated. **The cumulative incidence of fallers will be calculated as the total number of participants with first fall at each time point divided by the number of participants at risk.** A copy of radiograph confirming the fracture will be obtained.

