#### With:

#### **Primary endpoint:**

**Primary endpoint is the number of falls at 36 months.**

## Section: 15.2 Secondary Endpoints

Replace:

- (1) Change from month baseline at month 36 in osteocalcin;
- (2) Change from month baseline at month 36 in deoxypyridinoline;
- (3) Changes from baseline at month 36 in estradiol;
- (4) Change from month baseline at month 36 in endometrial thickness;
- (5) Nature, frequency and severity of adverse events and their relationship to treatment.

With:

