**Rationale:**

In the vast majority of cases, a hip fracture is a fragility fracture due to a fall or minor trauma in someone with osteoporotic bone. Risk factors of hip fractures observed are expected to be of long duration. However, BSYJF treatment was designed initially 36 months. Instead, a 10 year extension phase is added to explore the effect of transitioning from 36 months of treatment. The main objective of this extension phase is to evaluate if latent effects of BSYJF that might be lower fall rate and even hip fracture rate. In other words, 10 years extension follow-up of treatment cessation can be studied and is an accepted clinical approach.

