### Section: 3.3 Rational

Add:

**After the trial, the recruited participants will be followed up in the 3rd, 6th and 10th year to assess the latent efficacy of BSYJF interventions on number of falls in late postmenopausal women. The serum 25(OH)D levels will be also measured at those three time-points.**

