**All the included participants will be asked to record every number of fall during 10 years extension follow-up.**

Section: 15.2 Secondary Endpoints

Add:

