**Additional endpoint:**

**Number of falls at the end of 10 years extension follow-up will be performed by chi-square test.**

Section: 17.2 Diet and Exercise Control

Add:

During the entire trial, the subjects will be advised to follow the guideline for daily dietary intake and physical activities, such as intaking high-protein diet, avoiding alcohol abuse and smoking, and keeping active in daily physical activities. The questionnaire for daily dietary intake and physical activities should be recorded at 12, 24, 36 months during 36-month clinical trial **and at the 3rd, 6th and 10th year during 10-year follow-up.** Calcium and vitamin D supplement on their own should be prohibited in 36-month clinical trial.

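### The extension's falls endpoint has no stated start of counting, so on-treatment falls can enter the only measure of a post-treatment effect

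*Supplement*

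**What the plan says.** The Rationale of Amendment 2 states the purpose: "The main objective of this extension phase is to evaluate if latent effects of BSYJF that might be lower fall rate". The text added to Section 3.3 repeats it: "to assess the latent efficacy of BSYJF interventions on number of falls in late postmenopausal women". The revised Section 5.1 describes 36 months of treatment followed by a ten-year phase without treatment.

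The matching endpoint is item 8 of the Amendment 2 synopsis, "Number of falls at the end of 10 years extension follow-up". The addition to Section 15.2 gives the test: "Number of falls at the end of 10 years extension follow-up will be performed by chi-square test". Neither place gives a start date for the count.

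The counting rule is in Section 12.3, last replaced by Amendment 1: "Information about new falls while on study will be documented using form" and "The number of falls is accumulated". Amendment 2 does not alter that section. The primary endpoint is phrased in the same way ("Primary endpoint is the number of falls at 36 months") and is a running total to that time. The updated Table 1 has a single Falls row from baseline to year 10.

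One sentence points the other way. In the Section 9 addition, participants are asked to "record every number of fall during 10 years extension follow-up".

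The Amendment 2 synopsis also keeps all randomized patients in the analyses, with LOCF for data missing after baseline. Its eligibility section and the Section 6.2 addition exclude from the extension women who had large bone loss or a fragility fracture on treatment.

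**The concern.** A latent effect is a difference in falls after treatment has stopped. A count that runs from baseline adds 36 treated months to ten untreated years. If BSYJF reduces falls while taken and does nothing afterwards, that total still favours BSYJF, and the difference would be read as persistence.

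If women rather than falls are the unit, a woman who fell on treatment is already an event at month 36 and can tell us nothing about the later period.

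No planned analysis separates the two periods, so the extension's objective would rest on this one comparison. Two analysts could follow the plan faithfully and report different quantities, only one of which answers the question. The Amendment 2 description of changes gives study staff access to unblinded safety and efficacy data during the extension, so the window should not be left to be chosen later.

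**Working it through.** **The plan's own figure.** No sample size or effect is given for the extension endpoint. Section 11 gives 55 per group for falls, from 19% incidence in placebo, a 50% reduction, one-sided 5% and 90% power. The nearest reproduction adds three annual risks (57% v 28.5%) with a continuity correction: 57 per group (50 without it). Annual risks of 19% v 9.5% would need 231 per group, and compounded three-year risks of 46.9% v 25.9% would need 89. Dropout: 55/0.8 = 68.75, so 69 against the stated 70. The point does not depend on this calculation, but the time unit of the 19% is a reading: Section 11 attaches the word annual to the reduction only.

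**Inputs.** From the documents: 50% reduction, 19% incidence (read as annual), 70 per group, 3 years on and 10 years off treatment, two-sided 5%. Assumed: equal rates in both arms after month 36, constant Poisson rates, full follow-up unless stated.

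**Expected falls per woman, no latent effect.**
- Rate 0.19 per year: placebo 13 × 0.19 = 2.470; BSYJF 3 × 0.095 + 10 × 0.19 = 2.185; ratio 0.885. Treated-period falls are 0.57/2.47 = 23% of the placebo total.
- Rates from annual risks, −ln(0.81) = 0.2107 and −ln(0.905) = 0.0998: placebo 13 × 0.2107 = 2.739; BSYJF 3 × 0.0998 + 10 × 0.2107 = 2.407; ratio 0.879.

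**Rejection probability on fall counts, 70 per group.** With A and B the expected totals, z = (A − B)/√(A + B), and the probability is Φ(z − 1.96) + Φ(−z − 1.96).
- Rate 0.19: 172.9 v 152.95; z = 19.95/√325.85 = 1.105; probability 0.197. Simulation of 20,000 trials gave 0.197 and 0.202 in two runs.
- Rate 0.2107: 191.8 v 168.5; z = 23.3/√360.2 = 1.23; probability 0.233.
- Rate 0.19 with other on-treatment rate ratios: 0.104 for a ratio of 0.7 and 0.348 for 0.3.

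**Rejection probability on ever-fallers, rate 0.19.** By year 13, 1 − e^(−2.470) = 91.5% and 1 − e^(−2.185) = 88.8%. The pooled proportion is 0.9015, the standard error √(2 × 0.9015 × 0.0985/70) = 0.0504, and z = 0.0279/0.0504 = 0.55. The probability is 0.080 + 0.006 = 0.086; simulation gave 0.087 to 0.091. Over the same range of rate ratios it runs from about 6% to 13%.

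**Effect of LOCF.** If an assumed 20% to 40% of women have no extension data and keep their month-36 count, rejection rises to 26-32% on counts and 14-22% on ever-fallers.

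**Extension-only window, same truth, full follow-up.** Expected falls are 70 × 10 × 0.19 = 133 in each arm. The test rejects in 5.1% of trials on counts and 5.0% on fallers.

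**The case against.** The strongest reply is that inclusion of treated-period falls is nowhere stated. The accumulation sentence was already in place on 10 December 1999, before the extension was added on 10 January 2002, and so was written for a 36-month trial. The extension text speaks of recording falls during the ten years, of follow-up after the trial, and of a separate untreated phase with its own columns in Table 1. Falls at month 36 already have their own endpoint.

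This stands in part: an extension-only count is a permissible reading. But the Section 9 sentence is an instruction on recording that both readings require; it sets no analysis window. A reader might infer that the plan definitely counts treated-period falls. The documents do not go that far; they leave the start open beside a rule that accumulates.

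The second reply concerns size. The plan does not say whether the chi-square test compares falls or women. On women the inflation is small, because ten years of equal rates make nearly everyone a faller. That stands, and both figures are needed.

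The third reply is that a total from randomization fits the intention-to-treat statement better than a count restarted after post-randomization exclusions. That also stands, as a reason to report both, but the total does not measure a latent effect.

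**Conclusion.** The point holds as an undefined counting window whose only stated rule mixes on-treatment with post-treatment falls. Under the assumptions shown, the cumulative rate ratio is about 0.88 when the true extension ratio is 1.00. The chance of a spurious latent effect is about 20-23% on fall counts (10-35% across on-treatment rate ratios 0.7 to 0.3), or about 8-9% on ever-fallers, against 5% nominal.

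A reader might infer that such a trial would usually report a latent benefit. It would not: even on counts with the planned effect, more than three quarters of trials would not reach significance with full follow-up. The estimate is biased toward BSYJF either way.

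The figures rest on post-treatment rates that the documents do not give, on reading 19% as annual, and on Poisson falls. Severity is moderate: this is an additional endpoint of an exploratory extension, and the 36-month primary endpoint is unaffected.

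**What to change.** In the Amendment 2 synopsis (Endpoints and Statistical considerations) and in the Section 15.2 addition, define endpoint 8 as falls after the month-36 visit up to the year-10 extension visit. Restart the count and the person-time at month 36 for every woman followed in the extension, including those who fell on treatment. State that month-36 counts are not carried forward by LOCF into this endpoint. Report the total from randomization separately, as overall benefit.

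The cost is a few sentences and no new data, since the form in Appendix C dates each fall. There are two downsides. The comparison contains fewer falls than the 13-year total. And because women with large bone loss or fragility fracture on treatment are excluded from the extension, and treatment could affect those events, the comparison is not fully protected by randomization and should carry that caveat.

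The restart does not cure over-dispersion. If fall rates vary between women (assumed gamma variance 0.5 to 1), a chi-square test on fall counts still rejects in 16-26% of trials in the extension-only window, against 30-37% for the cumulative count. That needs separate attention.
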